### Data collection

After obtaining informed consent and/or assent, research assistants will collect sociodemographic and medical history information onto enrollment forms by face-to-face interview with study participants and/or their caregivers. Four psychosocial health questionnaires (described below) will also be completed at enrollment by study participants. Completion of the four questionnaires will be repeated at 12, 18, 24, and 36 months after enrollment, coinciding with the transfer time point, and 6, 12, and 24 months post transfer, respectively (Table 1). Blood viral-load sampling will be performed on the same schedule, and the results of all viral-load tests will be reported to clinic providers and filed in participants’ medical charts for use in HIV management. Per national treatment guidelines, stable patients who have been on HIV treatment for at least 6 months should have at least one viral-load test every year [31]. Clinic visits will also be tracked to measure the primary outcome of retention in care.

**Table 1 Tab1:** Adolescent Coordinated Transition (ACT) study timeline, visits, and procedures

Visit	Timeline	Study visit	Procedure	Intervention group	Control group
Enrollment	0 months	Yes	Enrollment	Yes	Yes
			Readiness assessment	Yes	Yes
			Psychosocial assessment^a^	Yes	Yes
			Viral load	Yes	Yes
Visit 1	3 months	Yes	Type of clinic	Pediatric clinic	Pediatric clinic
			Organized support group	Yes	No
			Readiness assessment	Yes	Yes
Visit 2	6 months	Yes	Type of clinic	Adult clinic	Pediatric clinic
			Organized support group	Yes	No
			Readiness assessment	Yes	Yes
Visit 3	9 months	Yes	Type of clinic	Pediatric clinic	Pediatric clinic
			Organized support group	Yes	No
			Readiness assessment	Yes	Yes
Visit 4	12 months	Yes	Type of clinic	Adult clinic	Pediatric clinic
			Organized support group	Yes	No
			Readiness assessment	Yes	Yes
			Viral load	Yes	Yes
Transfer to adult care					
Visit 5	15 months	No	Type of clinic	Adult clinic	Adult clinic
			Organized support group	Yes	No
Visit 6	18 months	Yes	Type of clinic	Adult clinic	Adult clinic
			Organized support group	Yes	No
			Viral load	Yes	Yes
Visit 7	21 months	No	Type of clinic	Adult clinic	Adult clinic
			Organized support group	Yes	No
Visit 8	24 months	Yes	Readiness assessment	Yes	Yes
			Psychosocial Assessment^a^	Yes	Yes
			Viral load	Yes	Yes
End Visit	36 months	Yes	Type of clinic	Adult clinic	Adult clinic
			Readiness assessment	Yes	Yes
			Psychosocial Assessment^a^	Yes	Yes

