The HLC tool has previously been validated by our research team among Nigerian ALHIV, and the MHC-SF has been validated among South African adolescents and adults [34, 40]. All the aforementioned tools will be administered by trained research assistants to study participants for a total of five times during the 3-year follow-up: at enrollment, transfer, and at 6, 12, and 24 months post transfer (Table 1). Additionally, healthcare transition readiness will be assessed twice (at enrollment and at transfer) using the Transition Readiness Assessment Questionnaire (TRAQ) [41, 42]. In a recent systematic review, the TRAQ was determined to be the best-validated transition tool with robust content and construct validity, as well as internal consistency [43].

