For secondary objective 2, the study will assess whether the ACT intervention leads to improvements in the social, emotional, and psychological wellbeing of study participants; improvements in their self-efficacy; or changes in their health locus of control (HLC) from an external to an internal locus of control. Additionally, ACT aims to understanding the potential of psychologically based intervening variables to influence important study outcomes (i.e., increased retention rates and suppressed viral load). To examine important temporal changes in psychological factors, mean changes will be calculated for HLC, FSSQ, MHC-SF, and SRBBS scores from the transfer baseline to 12 and 24 months post transfer. Additionally, between-group comparisons will be made using repeated-measures analysis of variance (ANOVA). Owing to multiple tests among the same subjects, an approximate type 1 error of .05 will be maintained either directly through the use of a technique designed to accommodate repeated-measures designs (e.g., RM-ANOVA), or through the use of post-hoc adjustment of *p* values (e.g., Bonferroni’s method).

Simultaneously, ACT will examine direct and indirect contribution of psychosocial factors on viral-load suppression and retention of study participants in both study arms through multiple mediation model analyses as recommended by Preacher and Hayes [45]. Mediation analyses are particularly useful in randomized control trials as they attempt to capture the effects or processes that occur after randomization. As noted by Preacher and Hayes, the multiple mediation model is preferred over the traditional simple mediation model [45]. Additional mediator/moderator models will also be explored in order to investigate the potential direct and indirect impacts of other ACT intervention components; these will include the use of peer-led support groups during the pre- and post-transfer period, and the relative impact of case management support on retention rates and viral-load measures.

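### Table 1 schedules the psychosocial questionnaires at three visits where the text citing it requires five, omitting transfer (month 12), the baseline for secondary objective 2, and month 18

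*Protocol article*

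**What the plan says.** **Text.** The schedule is given twice, and the two statements agree.

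- Outcome measures: the tools are administered "for a total of five times during the 3-year follow-up: at enrollment, transfer, and at 6, 12, and 24 months post transfer", with a reference to Table 1.
- Data collection: the questionnaires are completed at enrollment, and then "Completion of the four questionnaires will be repeated at 12, 18, 24, and 36 months after enrollment". Those months are equated with transfer and with 6, 12 and 24 months after it, again citing Table 1. Viral load is placed on the same schedule.

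**Table 1.** The row labelled "Psychosocial assessment", footnoted to the same four tools, appears at enrollment, visit 8 (month 24) and the end visit (month 36). Visit 4 (month 12) lists clinic type, support group, readiness and viral load. Visit 6 (month 18) lists clinic type, support group and viral load. Both are marked as study visits, and neither has a psychosocial row.

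**Analysis.** For secondary objective 2, the Statistical analysis section calculates mean score changes "from the transfer baseline to 12 and 24 months post transfer". It also plans a multiple mediation analysis in which "ACT will examine direct and indirect contribution of psychosocial factors on viral-load suppression and retention of study participants in both study arms".

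**The concern.** The schedule table and the text that cites it disagree on whether the questionnaires are given at transfer and six months later. The two time points in dispute carry weight in the analysis. Transfer is the baseline from which the secondary objective 2 changes are measured, and a score not taken then cannot be recovered later. Months 12 and 18 are also the only psychosocial measurements after enrollment that come before the 12-month retention window closes. A site working from Table 1 would collect neither. With twelve sites run by five implementing partners, different sites could also follow different versions of the schedule.

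**Working it through.** **Inputs**
- Text schedule: enrollment, transfer, and 6, 12 and 24 months post transfer (Outcome measures; Data collection).
- Transfer at month 12 after enrollment (Data collection; Table 1).
- Retention counted over the 12 and 24 months after transfer (Outcome measures), so the windows run over months 12–24 and 12–36.
- 216 participants and a total assumed loss of 22% (Sample size estimation).

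**1. The plan's own count.** Months 0, 12, 12 + 6 = 18, 12 + 12 = 24 and 12 + 24 = 36 make 5 administrations. The two text statements reproduce the stated five.

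**2. Count from Table 1.**

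| Procedure | Months in the text | Months in Table 1 |
|---|---|---|
| Psychosocial questionnaires | 0, 12, 18, 24, 36 (5) | 0, 24, 36 (3) |
| Viral load (same schedule) | 0, 12, 18, 24, 36 (5) | 0, 12, 18, 24, 36 (5) |

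The stated five is not reproduced from the table cited for it. The viral-load rows are complete at all five times, so two psychosocial rows lost in reading the PDF is an unlikely explanation.

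**3. Size of the gap.** Missing months: 12 and 18, that is 2/5 = 40%. Planned questionnaire sets before attrition: 216 × 5 = 1,080 by the text and 216 × 3 = 648 by Table 1, a difference of 432. If all of the assumed 22% loss had already happened by month 12, the difference would be 432 × 0.78 ≈ 337.

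**4. Secondary objective 2.** Write S(m) for a score at month m. The defined changes are S(24) − S(12) and S(36) − S(12). Under Table 1, S(12) does not exist, so neither can be formed. S(24) − S(0) remains available but is a different quantity, because it includes change during the 12-month transition period.

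**5. Mediator timing.** Psychosocial scores available from month 12 onward:

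| Cut-off | Text schedule | Table 1 |
|---|---|---|
| By the opening of the retention window (month 12) | 12 | none |
| Before the 12-month window closes (month 24) | 12, 18 | none |
| Before the 24-month window closes (month 36) | 12, 18, 24 | 24 |

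Under Table 1, no score after enrollment precedes the close of the 12-month window or the viral-load test at month 24. For the 24-month outcomes one such score remains, at month 24, when half of the window has passed.

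**The case against.** The best defense is that the intended schedule is clear. It is stated twice, once in months and once relative to transfer, and the analysis relies on a transfer score, so Table 1 is the outlier. The table has other signs of incompleteness: visit 8 shows no clinic-type or support-group row, and the end visit shows no support-group row although the group continues to 24 months post transfer. The schedule figure (Fig. 4) is not shown and may list all five assessments. Sites following the text would lose nothing. All of this stands, and it makes the loss conditional. It does not remove the conflict between the text and the table it cites.

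A reader might infer more than the documents support.

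- *That month 12 is the only usable mediator score.* In the text schedule, month 18 also precedes the close of the 12-month window. In Table 1 itself, month 24 precedes the close of the 24-month window.
- *That month 12 is a post-intervention score, and the mediator should be fixed there.* The support group runs on to 24 months post transfer, so month 12 falls during the intervention. The plan also wants to explore support groups before and after transfer, and does not say which score is the mediator. That choice can be left to the analysis plan.
- *That later scores would be mostly missing for adolescents not retained.* The article gives no figure for this. Research assistants administer the tools, and follow-up of non-attenders is not described. Harder collection is a reasonable worry, not a stated fact.

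The impact is also bounded. Under Table 1, enrollment and both outcome time points of secondary objective 2 remain, so a between-arm repeated-measures comparison could still be made.

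**Conclusion.** The contradiction is real: five administrations in the text, three in the table cited for them, with months 12 and 18 missing from the table. Given that sites follow Table 1, the changes from transfer in secondary objective 2 cannot be computed as defined. The mediation analysis is then weakened: it has no score after enrollment that precedes the close of the 12-month outcome window, and only one, midway through the window, for the 24-month outcomes. It would not be wholly impossible.

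The size is 40% of planned administrations, at most 432 sets for 216 participants, and about 337 if all of the assumed loss came before month 12. The primary retention analysis rests on clinic visits and is not affected. The conclusion assumes that Table 1 was extracted intact, which the complete viral-load rows support, and it could not be checked against Fig. 4. Because the discrepancy changes which data are collected, it is more than a clerical slip.

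**What to change.** Reconcile Table 1 with the Data collection, Outcome measures and Statistical analysis sections by adding the psychosocial assessment at visit 4 (month 12) and visit 6 (month 18) in both arms. Confirm that Fig. 4 and the site working documents agree. Recruitment began in the week of 26 June 2017, so the first month-12 visits fall around late June 2018; the corrected schedule should reach all twelve sites before then.

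The cost is two added table rows and a notice to sites. Both visits are already study visits with blood drawn for viral load, and the text already commits to the questionnaires there, so no visit is added. The readiness assessment could be reconciled in the same edit: the Outcome measures section has it done twice, while Table 1 lists it at seven visits (months 0, 3, 6, 9, 12, 24 and 36).

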### Sample size estimation

The design requires two arms (control = direct transfer without transition period or OSG and intervention = graduated transition with OSG). Six geopolitical zones are included in the design, with two sites (one replicate per arm) located in each zone. The factors considered for the sample size estimate are: at least 80% power, assuming 20% effect size, a confidence level of 95%, a correlation among repeated measures of 0.3, and an intra-class correlation within clusters of 0.05. Further, we assume equal numbers of clusters between CG and IG, and clusters within those conditions to be of equal size. Based on these assumptions, a baseline number of 15 participants per site was needed. This was, however, adjusted for several assumed losses. Based on knowledge of healthcare in this area and among target participants, the following participant loss estimates were made: healthcare transfers out of study sites at 5%, participant moving out of study area at 5%, deaths during the study at 7%, and study withdrawal/dropout at 5%. This results in a total of 22% dropouts, requiring an additional three participants (15 × 0.22) for a total of 18 participants per site. Additionally, we anticipate a 30% rate for declining to participate. Hence, we will need to approach an additional five ALHIV (18 × 0.3) for a total of 23 ALHIV currently enrolled as taking ART at study initiation to ensure that the requirement of 18 participants per site is met. Therefore, for two arms across six zones, we have a recruitment goal of 276 ALHIV (23 × 2 × 6) with a desired final sample size of 216 ALHIV (18 × 2 × 6) consented to participate. Sample size estimation was performed using G*Power (v. 3.1.9.1, Universität Düsseldorf, Germany) and Sampsize (v 0.6, P. Glaziou, ampsize.sourceforge.net) with appropriate adjustments for cluster randomization [44].

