### Site selection and randomization

Study sites were selected from among secondary- and tertiary-level PEPFAR-supported healthcare facilities with at least 12 months’ experience in providing comprehensive HIV care and treatment services. Eligible sites were further expected to meet the following criteria:At least 20 ALHIV enrolled in care as of 31 July 2016Separate pediatric and adult HIV care teams and clinicsAt least one dedicated physician and one dedicated nurse for each pediatric and adult HIV clinic

All sites were assessed using a standardized tool to determine whether they met the selection criteria.

Our desire was to meet the suggestions of the Consolidated Standards of Reporting Trials (CONSORT) “extension for cluster designs” checklist in our randomization procedure. To that end, we provide details here of both sequence generation and allocation [29]. Twelve healthcare facilities were selected and randomized 1:1 to the intervention and control arms (Fig. 2). These 12 study sites were pair-matched by geographic location and level of care and then randomly assigned to the intervention group (IG) or to the control group (CG). Particular attention was paid to remove bias of group assignment by concealment at the individual participant level. The randomization of facilities was carried out using scripting language in R (v. 3.3.2) by the project statistician [30]. We first created a random number between 1000 and 10,000 and used the result to seed the group assignment so that the results would be reproducible. Based on the pair-matched locations and level of care, we used the “sample” function to determine which member of each matched facility pair would be assigned to each of CG and IG. Of note, age at transfer for each study site was considered in order to include sites that transferred at 15 years as well as 18 years, according to the results of our survey [14]. All enrolled study participants receiving care at each study site will follow the procedures of their respective randomization arms described below.

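### The site-eligibility floor of 20 ALHIV is below the 23 per site that the sample-size section relies on, and 23 is itself too few at the stated refusal and loss rates, so 18 per site (216 in total) is not secured

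*Protocol article*

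**What the plan says.** Protocol article, Sample size estimation. The calculation is for "at least 80% power, assuming 20% effect size, a confidence level of 95" per cent, with "a correlation among repeated measures of 0.3, and an intra-class correlation within clusters of 0.05". It assumes equal numbers of clusters in the two arms, and "clusters within those conditions to be of equal size". From these inputs "a baseline number of 15 participants per site was needed".

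Two inflation steps follow. For 22% loss the plan adds three, "requiring an additional three participants (15 × 0.22) for a total of 18 participants per site". For 30% refusal it adds five (18 × 0.3), giving "a total of 23 ALHIV currently enrolled as taking ART at study initiation", which it says will ensure 18 participants per site. Over 12 sites this is 276 approached and 216 consented.

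Protocol article, Site selection and randomization. A facility qualifies if, among other criteria, it has at least "20 ALHIV enrolled in care as of 31 July" 2016. This criterion sets no limit on age band, ART use, awareness of diagnosis or closeness to transfer.

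The eligibility criteria and the description of the intervention do set such limits: age 13 to 17, taking ART, aware of the diagnosis, medically stable, and about one year below the site's transfer age of 15 or 18. Under Participant recruitment, site staff compile a master list of eligible ALHIV aged 13 to 17 at each site.

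**The concern.** The site criterion is the only stated rule that bears on how many participants each cluster can supply, and it is set below the number that the sample-size section says is needed. It also counts a wider population than the one that can be enrolled: the Study setting section uses 10 to 19 years when it counts ALHIV. The count date is about 11 months before recruitment opened in the week of 26 June 2017.

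Separately, both inflation steps multiply by one plus the rate, although each rate applies to the larger starting number. The targets of 18 and 23 therefore fall short even if every site meets them.

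At stake are the 15 evaluable participants per site, and the equal cluster sizes, on which the stated 80% power rests.

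**Working it through.** **Inputs, all from the article.** Site floor 20; base 15 per site; total loss 22%; refusal 30%; 12 sites, six per arm; ICC 0.05.

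**1. The plan's own chain, reproduced.**
- 15 × 0.22 = 3.3, taken as 3, so 18 consented per site.
- 18 × 0.3 = 5.4, taken as 5, so 23 approached per site.
- 18 × 12 = 216 and 23 × 12 = 276, as stated.

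The base of 15 can be approximated only by adding assumptions. Reading the 20% effect size as f = 0.20 in a between-group repeated-measures ANOVA with three measurements (neither is stated) gives N = 108. The design effect 1 + 14 × 0.05 = 1.70 takes this to 183.6, or 15.3 per site. Power at 15 per site is then 0.797.

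**2. The chain run forward at the stated rates** (consented = approached × 0.70; evaluable = consented × 0.78).

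| Starting point per site | Consented | Evaluable | Consented, 12 sites |
|---|---|---|---|
| Plan's stated targets | 18 | 15 | 216 |
| 18 consented, if achieved | 18 | 18 × 0.78 = 14.0 | 216 |
| 23 approached | 23 × 0.70 = 16.1 | 16.1 × 0.78 = 12.6 | 193 |
| 20 approached (the floor) | 20 × 0.70 = 14 | 14 × 0.78 = 10.9 | 168 |

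The last row assumes that all 20 are eligible. Its total of 168 would arise only if all 12 sites sat exactly at the floor. Even under the plan's additive method, 20 / 1.3 = 15.4, still below 18.

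**3. Where the gap comes from.** Of the 4 consented lost between 18 and 14, 18 − 16.1 = 1.9 come from the inflation step and 16.1 − 14 = 2.1 from the floor. Of the 4.1 evaluable lost between 15 and 10.9, 2.4 come from inflation and 1.6 from the floor (rounded).

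**4. Inflation by division.**
- 15 / 0.78 = 19.2, so 20 consented for 15 evaluable.
- 18 / 0.70 = 25.7, so 26 approached for 18 consented.
- To carry 20 consented through, 20 / 0.70 = 28.6, so 29 approached.

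**5. Illustrative power.** Assumed: 70% v 90% retained, alpha 5%, noncentral t with 12 − 2 = 10 df. The design effect is DE = 1 + (m − 1) × 0.05. The standard error is SE = √[(0.7 × 0.3 + 0.9 × 0.1) × DE / (6m)], and the noncentrality is 0.20 / SE.

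| m evaluable | DE | SE | 0.20 / SE | Two-sided | One-sided |
|---|---|---|---|---|---|
| 15 | 1.70 | 0.0753 | 2.66 | 67% | 80% |
| 12.6 | 1.58 | 0.0793 | 2.52 | 62% | 76% |
| 10.9 | 1.50 | 0.0828 | 2.42 | 59% | 73% |

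Under the f = 0.20, three-measurement reading, the same move from 15 to 10.9 lowers power from 0.797 to 0.717.

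**6. Unequal size alone.** With DE = 1 + ((1 + CV²)m − 1) × 0.05 and an assumed CV of 0.3, DE at m = 15 is 1.77. Two-sided power goes from 66.9% to 65.2% at m = 15 and from 58.8% to 57.4% at m = 10.9, a cost of 1 to 2 points.

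**The case against.** The best defence is that 20 is a minimum for screening sites, not a forecast of enrolment, and that it refers to an earlier date than the 23. A lower screening floor need not contradict a higher recruitment target. Nothing shows that any selected site has only 20. The implementing partners' totals (over 24,000 ALHIV in more than 850 clinics) average roughly 28 per clinic, although that crude figure covers ages 10 to 19 and says nothing about these 12 sites. Larger sites could also enrol more than 18, since no cap is stated, and actual counts may stand in the full protocol or in the site-selection flow diagram, which is not shown here.

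Most of this stands. A reader might infer that the trial will enrol only 168, or that its power is 59%. The documents support neither. The first needs every site at the floor; the second also needs assumed retention rates and a two-sided test, whereas the Statistical analysis section names a one-way test and the effect-size scale is undefined. That two-sided model gives only 67% at the plan's own 15 per site, so most of its distance from 80% comes from its assumptions. With 75% v 95% one-sided, 10.9 per site would still give 81%.

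A reader might also infer that equal cluster size is the damaging assumption. It is a common simplification, it belongs to the calculation of 15 rather than 18, and at this ICC it costs little.

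The defence does not reach two facts. The stated selection rule leaves the required number per site unsecured, and 23 approached at 30% refusal gives 16.1, whatever the site sizes are.

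**Conclusion.** The point holds as a failure to secure the stated size, not as a prediction of shortfall. The floor of 20 is below the plan's own 23 and counts ALHIV who may not be eligible. A site at the floor would give 14 consented and about 10.9 evaluable, against targets of 18 and 15, and that is a worst case only in the sense that all 20 must first be eligible and actual sites may be larger.

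The inflation error does not depend on site size. At the stated rates, the recruitment goal of 276 yields about 193 consented rather than 216, and 216 consented would leave 14.0 evaluable per site rather than 15.

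The effect on power is moderate: about 7 to 8 points between 15 and 10.9 evaluable per site in each model tried, less for any mix of larger sites. The absolute levels rest on assumed retention rates, sidedness or effect-size reading, and should not be quoted as the trial's power. The main problem is numbers; imbalance is secondary. This should be corrected, but it does not undermine the design.

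**What to change.** Leave the selected sites as they are; rewriting the eligibility floor would change nothing now that they are chosen. Instead:

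- Take the number of eligible ALHIV at each site from its master list, after the age, ART, disclosure and transfer-timing limits.
- Multiply by 0.70 and then by 0.78, and report expected consented and evaluable numbers by site and in total.
- Correct the inflation by dividing: 20 consented per site for 15 evaluable, and 26 approached for 18 consented.
- Replace the equal-size assumption with the observed mean m and CV, and restate power with the design effect 1 + ((1 + CV²)m − 1) × ICC.
- Define the 20% effect size, and state power for that definition and for the sidedness of the planned test.

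The cost is a recalculation and probably a less favourable stated figure. The restatement itself adds no patients.
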